## Abstract

**Introduction:**

There are several known risks relating to poor nutrition during pregnancy, including the development of complications and poor birth outcomes. While food insecurity is associated with poorer nutrition, data on the prevalence and severity of food insecurity in pregnancy in the UK is lacking. This study aims to explore the prevalence, experiences and health impact of food insecurity in pregnancy in England to develop strategic recommendations for intervention strategies.

**Methods and analysis:**

Food, Pregnancy & Me is an observational, multi-method study. Questionnaires exploring diet quality, food security, mental health, and other health behaviours will be distributed to all women and pregnant people in their third trimester in two NHS Trusts in England (North East and West Midlands). Returned questionnaires (n=605) will be linked to routine maternal and birth outcome data and pseudo-anonymised. We will estimate the prevalence of food insecurity in pregnancy in these locations, associations with diet quality, maternal mental health, and pregnancy outcomes (e.g., pre-term birth, pre-eclampsia, gestational diabetes). Qualitative interviews (n=40) with participants identified as having experienced food insecurity will explore their lived experience, support received, and recommendations for additional support needs. Through a series of co-production workshops with local and national system shapers and experts by lived experience, we will use the data gathered to produce strategic recommendations for intervention with pregnant women and people facing food insecurity. We will then explore the potential costs and benefits of implementing the proposed recommendations.

**Ethics and dissemination:**

Ethical approval was obtained from Newcastle and North Tyneside 1 NHS Research Ethics Committee (24/NE/0027). Findings will be disseminated to key national and local system shapers and policy makers, advocacy groups, and the public through reports, presentations, the media and open access publications.

**Study registration number:**

ISRCTN16655955

## Introduction

Food insecurity (FI) exists when a person lacks regular, socially and culturally acceptable, access to safe and nutritious food for normal growth and development and an active and healthy life [1]. FI prevalence has increased across high-income countries, and the United Kingdom (UK) is no exception [2]. Monitoring households in the UK estimates the prevalence of moderate/severe FI to be around 10%, with a further 7% experiencing marginal food security [3], with substantial geographic and socio-demographic variations. For example, higher rates are seen in households with children (especially those with more than three children), amongst those households with a person limited by a disability, in minoritised ethnic groups, and living in the North East of England [4,5].

FI is associated with nutritionally inadequate diets, which are often high in energy-dense and high fat, salt and sugar, processed food [6–8]. The health impact of a poor diet on an individual has been well established, with increased risk of developing various chronic diseases, including cardiovascular disease and Type 2 diabetes [6–13]. FI has been further associated with high levels of stress, anxiety, depression and sleep difficulties [14–20].

Pregnancy is a life course stage with increased nutritional requirements to support the health of the mother and the development of the infant [21,22]. This means that pregnant women or people, and their children, are particularly vulnerable to the physical and mental health impacts of FI. The consequences of suboptimal nutrition during pregnancy can be significant, in the short- and long-term, for both mother and child. FI during pregnancy has been shown to be associated with a range of adverse outcomes such as gestational diabetes mellitus, mood disorders, inadequate or excessive weight gain, and neonatal mortality [23,24]. In addition, research has highlighted that epigenetic modifications which occur due to inadequate nutrition in pregnancy can have life-long implications for the infant, including an increased risk of obesity, cardiovascular disease and Type 2 diabetes. [25–29]. Despite these stark health implications, research with women in households experiencing FI reports coping mechanisms such as women restricting their own food intake in favour of their children and other household members [19,20,30–32]. Public health policy and interventions are needed during this key life course stage to ensure availability of nutritious culturally appropriate food, to promote the best start in life, and to mitigate the harmful impacts of environmental exposures to inequalities which occur in utero, such as FI.

Whilst FI in England is currently monitored at the population level by various Government departments [3,33] and charities [5,34], little is known about the current prevalence, drivers and mitigators of FI during pregnancy in England. Questionnaires used for FI monitoring through nationally representative surveys do not include questions about respondents’ pregnancy status, and even if such questions were included, numbers would likely be too small to obtain reliable prevalence estimates. Potential pregnancy-related factors are also not captured. As a result, most of the evidence on food insecurity and pregnancy to date comes from the USA and Canada [23,35]. This study aims to determine the prevalence of FI in two geographically and socio-economically diverse regions of England, to understand the experiences and health impacts of those who have faced FI during pregnancy and establish policy and practice recommendations to address FI during this crucial life course stage.

## Methods

### Study aim and objectives

This study aims to explore the prevalence, experiences and health impact of food insecurity in pregnancy in England and co-develop strategic recommendations for intervention strategies. This will be achieved by:

Quantitatively measuring FI in the third trimester of pregnancy to estimate prevalence and its association with socio-demographic characteristics (Phase I).Linking pregnancy FI data with routine pregnancy health records for the mother and the baby to estimate associations between FI (and severity) with maternal and child health (Phase I)Quantitatively collecting maternal diet quality data in the third trimester to explore associations between FI (including severity) and maternal diet quality (Phase I)Qualitatively exploring the experiences of women experiencing FI in pregnancy and their support/intervention needs (Phase II)Working with a range of stakeholders/system shapers, and the evidence generated in phases I and II, to co-produce strategic recommendations for holistic provision of support for women and pregnant people experiencing FI during and after pregnancy (Phase III).Assessing the costs and benefits of implementation of the strategic recommendations for intervention support to help decision makers plan future services and interventions (Phase III)

### Study design and setting

This observational, multi-method study, consists of three phases. Phase I is a survey of women and pregnant people in their third trimester. Participants in their third trimester will be able to report experiences of food insecurity throughout their pregnancy. Data will be collected on their diet quality, food security, mental health, and tobacco/e-cigarette use. Survey data will be linked to data from routine maternity records, including data on maternal health during pregnancy (e.g., pre-eclampsia, gestational diabetes) and childbirth outcomes (e.g., birth gestation, birth weight, and Apgar score). Phase II involves interviews with those identified by the research team from the survey response as having experienced FI. The interviews will explore their lived experience, the support they received, and their recommendations for additional support needs when facing FI in pregnancy. Fig 1 shows the SPIRIT schedule of enrolment, interventions, and assessments for participants in Phases I and II.

**Fig 1 pone.0321638.g001:**
[figure not shown]
SPIRIT schedule of enrolment, interventions, and assessments.

Phase III will co-produce strategic recommendations for interventions and services working with women and pregnant people facing FI and determine the costs and benefits to implementation of these recommendations compared to standard practice. Fig 2 shows the flow of the study phases.

**Fig 2 pone.0321638.g002:**
[figure not shown]
Flow of study phases.

### Study setting

The study will be conducted in two NHS Trusts: one in the North East and one in the West Midlands of England. These regions were chosen due to their high prevalence of FI, deprivation, and demographic diversity. For example, compared to other regions in England, the North East has the highest prevalence of FI (12% experiencing low/very low food security, compared to 6% in the East of England) [36] and the West Midlands has over 40% the population from ethnicities other than White British (compared to a national average of 18%) [37,38].

### Phase I: The survey

This will be a prospective study with data linkage to routine maternity records. The survey will include quantitative data that are not routinely collected by maternity services and will be linked to maternal and child health record data with a unique ID number for each participant. Data linkage to routine maternal and child health records will take place following delivery and discharge from maternity care. All routine maternity data will be pseudo-anonymised using the unique participant IDs before sharing with research team members outside of NHS Trusts.

### Eligibility criteria

All adult women and pregnant people in their third trimester of a viable pregnancy (28–40 weeks gestation) who register for maternity services based at Queen Elizabeth Hospital Gateshead or University Hospital Coventry will be invited to take part in the study. Those under 16 years old, non-residents in the UK, less than 28 weeks gestation, post-partum, or receiving care by maternity services other than those based at Queen Elizabeth Hospital Gateshead or University Hospital Coventry, will be excluded from the study. Survey respondents will receive a £20 voucher upon completion of the questionnaire.

### Sample size

As prevalence of FI in pregnancy has not previously been explored in the UK context, accurate prevalence data on which to base sample size calculations is not available. We have therefore used the following prevalence estimates to inform the sample size calculations: FI prevalence of up to 30% (extrapolated from UK general population estimates which use different measurement tool for FI than in our study [5]); birth per year of 1800 at Gateshead Health Foundation Trust and 6000 per year at University Hospitals Coventry and Warwickshire [39]; 10% prevalence of antenatal depression [40]; and 7–8% prevalence of pre-term delivery [41]. Based on these estimates, and a confidence level of 95%, margin of error of 5%, and estimated attrition rate of 4%, the required sample size is 605 participants. We will aim to achieve approximately equal numbers of participants at each site.

### Recruitment

Each NHS Trust will distribute recruitment packs to all women and pregnant people entering their third trimester in their locality. The recruitment pack will contain a cover letter and information on how to obtain the study information in other languages, participant information sheet (PIS), questionnaire, pen, self-addressed envelope, and a leaflet highlighting local food aid, financial support and mental health support services. There will also be a QR code and website link to a participant information video to support those with low English literacy levels. The questionnaire will also be available to complete online. The rationale for this sampling technique is to be inclusive of all adult pregnant people and obtain information on the prevalence of FI in this population. To enhance recruitment, the study will also be promoted in maternity unit waiting areas via posters and targeted reminders sent through NHS communication routes (e.g., text messages or usual maternity notes application push notifications).

The challenges of recruiting participants reflective of the background pregnant populations in these locations has not been underestimated. Aggregated demographic statistics on the maternity population for the previous year will be extracted by the maternity teams in each NHS Trust. The demographic characteristics of survey respondents will be regularly monitored and compared against these aggregated statistics. Where imbalances arise, these will be discussed with the study management group (SMG) and study steering committee (SSC) to determine if supplementary recruitment methods should be employed. These supplementary methods include:

Face-to-face recruitment for those attending general hospital-based appointments.Face-to-face recruitment from community midwife clinics located in areas where under-represented groups receive their care (e.g., areas of highest deprivation or geographies with high case load of minoritised ethnic groups).

### Outcome data collection

Return of the questionnaire will act as consent for inclusion in both the survey analysis and data linkage to maternity records and is made explicit in the participant information sheet and the questionnaire cover page.

The primary outcomes for this study are maternal antenatal depression and infant pre-term delivery (<37 weeks gestation). As antenatal depression assessments are only routinely implemented in standard care where depression is indicated on the Whooley screening questions, the Edinburgh Postnatal Depression Scale [42] will be included in the questionnaire to ensure an assessment is available for all participants. Infant pre-term delivery (less than 37 weeks gestation) will be obtained from routine maternity records.

To obtain an estimate of the prevalence of FI in this population, participants will complete the 10-item USDA Food Security Survey Module (USDA FSSM) using a 30-day recall period [43]. This questionnaire was developed in the USA and has been validated and used in different countries/contexts, including the UK [44]. Additional questions on FI stability, barriers to utilisation of food, and food coping strategies specific to pregnancy will explore further aspects of the FI experience among women and pregnant people [45].

Further data will be collected using the following questionnaires:

*Diet quality:* An adapted version of the Brief Diet Quality Assessment Tool (BDQAT) [46] will be used. Adaptations to the original tool were made, in consultation with experts by lived experience to ensure acceptability to a variety of people, including those who are on a low-income, from a minoritised community, or pregnant. Adaptations included, adding sausages and burgers (animal source unspecified), removing alcohol, and adding example food items that are more commonly consumed in several minoritised communities in the UK (e.g., different types of bread (lavash, kulcha, chapatis) and sweet foods (jalebi, halwa, sweet valenki)). Open ended questions have been included to enable participants to describe any differences in their diet during pregnancy and in the preconception period.*Socio-demographic characteristics:* Routine maternity data does not include many of the individual level socio-demographics that would be relevant to the food insecure context. Questions relating to education, employment, receipt of benefits (including those specific to pregnancy such as healthy start vouchers, and more general benefits such as universal credit, personal independence payment), income, support networks and household occupancy will be included.*Health behaviours:* Questions related to health behaviours relevant to pregnancy have also been included. These include questions about smoking, vaping, and intentions regarding breastfeeding.

### Data linkage

Routinely collected relevant data will be exported from the electronic patient records and linked using NHS numbers and unique participant identification numbers for each participant. Table 1 shows the data that will be extracted from routine records.

**Table 1 pone.0321638.t001:** Data extracted from maternity records to be linked to the survey data.

Maternal Outcomes	Child outcomes
Gestational diabetes	Birth weight
Preeclampsia	Gestational age at delivery
Pregnancy induced hypertension	Large- and small-for gestational age
Induction	Breastfeeding initiated/at discharge from maternity services
Mode of delivery	Admission to special care baby units (and length of stay)
Length of stay in maternity unit	Apgar score at 1 and 5 minutes
Age	
Parity	
Body Mass Index	
Ethnic group	
Deprivation score (index of multiple deprivation (IMD) scores)	
Alcohol and illicit drugs	
Any relevant previous medical history (e.g., history of depression, previous pregnancy health such as low birth weight)	

### Data analysis

A binary food security status will be calculated for each participant according to the thresholds described by the USDA Household Food Security Survey Module [43]. Additionally, an ordinal variable will be calculated to determine sub-groups of high, moderate, low, and very low food security. Diet quality scores will also be calculated. The Edinburgh Postnatal Depression Scale will also be scored and binary variable will be generated with scores above 12 indicating antenatal depression.

Multivariable logistic regression models (binary and ordinal) will be used to examine associations between food security status and severity with health outcomes in pregnancy. The models will include socio-demographic and clinical factors related to both food security and health outcomes in pregnancy, such as age, deprivation score, ethnicity, employment status, smoking status, and household occupancy. We will explore differences between food security and maternal and child outcomes across socio-demographic characteristics by adding the relevant interaction terms to the developed models. If more than 5% of data are missing from demographic variables, multiple imputation methods will be used and sensitivity analyses conducted. All analyses will be carried out in STATA v.18.

Furthermore, open-ended questions included in the questionnaire will be analysed thematically to explore the impact of food security status in relation to pregnancy diets and health outcomes.

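### No analysis of the full EPDS score is named for the antenatal depression outcome; a key full-score analysis beside the split above 12 would recover information already collected

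*Protocol article*

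**What the plan says.** All statements are in the protocol article.

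- **Outcome data collection** makes maternal antenatal depression and pre-term delivery the primary outcomes. It puts the EPDS in the questionnaire because routine care assesses only women who screen positive. A total score is therefore collected from every respondent.
- **Data analysis** reduces that score to two categories: "The Edinburgh Postnatal Depression Scale will also be scored and binary variable will be generated with scores above 12 indicating antenatal depression".
- The same section names the models: "Multivariable logistic regression models (binary and ordinal) will be used to examine associations between food security status and severity with health outcomes in pregnancy". It lists adjustment factors such as age, deprivation, ethnicity, employment, smoking and household occupancy. It adds interaction terms for socio-demographic characteristics and defines a four-level food security variable.
- **Sample size** plans on "10% prevalence of antenatal depression" and a food insecurity prevalence of at most 30%, with 95% confidence, a 5% margin of error and 4% attrition. It concludes that "the required sample size is 605 participants". It states no power, target effect, EPDS mean or EPDS standard deviation.

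**The concern.** Splitting a score at a point that only about one participant in ten exceeds treats everyone on the same side of the cut as identical. Scores of 0 and 12 count the same, as do 13 and 30. Much of the information about whether food-insecure women have more depressive symptoms lies in differences that the split ignores.

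At the planning prevalence, about 58 participants (0.10 × 581) would be above the cut. Those 58 events must support an adjusted model with at least six named factors, some with several categories, plus interaction terms and comparisons across severity levels. The loss matters most for the interaction and severity questions, because each rests on only part of the 58 events. The total score is already collected, so a more precise analysis needs no further data.

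**Working it through.** **1. The plan's own figure.** For a prevalence p = 0.30 with margin 0.05:

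n0 = 1.96² × 0.30 × 0.70 / 0.05² = 322.7

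A finite population correction, n0 / (1 + (n0 − 1)/N), uses the annual births at each site:

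- N = 1800: 322.7 / (1 + 321.7/1800) = 273.8
- N = 6000: 322.7 / (1 + 321.7/6000) = 306.3

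The sum is 580.0, or 581 if each site is rounded up. Dividing by 0.96 gives 604.2 to 605.2, which matches 605. The figure is a two-site precision calculation for food insecurity prevalence. The 10% depression prevalence is not needed to reach it.

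**2. Inputs for the comparison.**

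- From the article: 605 × 0.96 = 581 analysable; food insecurity at its upper planning value of 30%, giving 174 exposed and 407 unexposed; 10% above the cut overall; two-sided 5% level.
- Assumed, not in the documents: a normal score with equal SD in both groups, no covariate adjustment, and a mean difference of d SD, varied below.

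**3. Information kept by the split.** For small effects and a normal score cut where 10% lie above (standard normal point 1.2816), the efficiency relative to the full score is

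φ(1.2816)² / (0.10 × 0.90) = 0.34

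where φ is the standard normal density. Since 581 × 0.342 = 199, the split carries roughly the information of 200 participants with full scores. This ratio does not depend on d.

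**4. Power.** Full score: Φ(d × √(n1·n2/n) − 1.96), with √(407 × 174/581) = 11.04. At d = 0.30 this is Φ(3.312 − 1.96) = Φ(1.352) = 0.912.

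Split: the cut is placed so that 10% lie above it overall. At d = 0.30 this gives 8.3% in the food-secure and 13.9% in the food-insecure, an odds ratio of 1.78. The two-proportion test with pooled variance under the null has standard errors 0.0272 (null) and 0.0296 (alternative). Its power is Φ((0.0560 − 1.96 × 0.0272)/0.0296) = 0.537.

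| Assumed difference (SD) | Full score | Split above 12 |
|---|---|---|
| 0.20 | 60% | 28% |
| 0.25 | 79% | 41% |
| 0.30 | 91% | 54% |
| 0.35 | 97% | 66% |
| 0.40 | 99% | 77% |

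**5. Lower food insecurity prevalence, d = 0.30.** At 20% exposed, 82% vs 47%. At 10% exposed, 58% vs 34%.

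**6. Skewed scores.** Simulation with rounded normal scores at d = 0.30 returned 91% vs 54%. With right-skewed (gamma) scores at a nominal 0.30 SD, a t-test on the full score against the split gave 91% vs 24% for an additive shift and 85% vs 63% for a multiplicative one. Over nominal effects of 0.20 to 0.40 SD the gap ran from 13 points (97% vs 84%) to 67 points (91% vs 24%). With a rank test on the full score instead, it ran from 8 points (45% vs 37%) to 75 points (99% vs 24%). The full score had the higher power in every scenario tried.

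**The case against.** **The cut-off is a legitimate outcome definition.** The primary outcome is a clinical category, the sample size section plans on its prevalence, and the threshold is fixed in advance. Replacing it would change the question from risk of depression to mean symptom level. This stands: the split should remain as the analysis that defines antenatal depression.

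**A reader might infer that the plan itself drops power from 91% to 54%.** The documents do not support that. They state no effect size, standard deviation or power. That pair is one row of a table that rests on an assumed difference, a normal score, the upper planning prevalence and no adjustment.

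**A reader might also infer that the study falls short of its power.** It sets no power target. Its size comes from the precision of a prevalence, and that figure reproduces.

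**A reader might take the ordinal model to place food security severity on the outcome side,** since neither primary outcome is ordinal as defined. The text does not say which variable is dependent. An ordinal model could serve an outcome such as the Apgar score, or the EPDS total itself. The wording is ambiguous, not wrong.

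**A reader might conclude that diet quality, birth weight and gestational age must also be split.** The article says nothing of the kind. It says diet quality scores will be calculated and does not rule out other models. A condensed article commonly leaves such models to the full plan.

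**A full-score analysis may already be in a plan not shown.** That is possible, and the article says the scale will be scored. But the split and the logistic models are what it states for this primary outcome, so a full-score analysis would be an addition to it.

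**Conclusion.** The point holds as an inexpensive improvement, not as an error in the plan. The article collects a full EPDS score from everyone, states only the split above 12, and names only logistic models. The finding that the split keeps about one third of the information rests on a roughly normal score and the article's own 10% prevalence. The power figures rest in addition on the assumed differences, 30% food insecurity and an unadjusted comparison. Under the normal model at 30% food insecurity the gap is about 22 to 38 percentage points for differences of 0.20 to 0.40 SD. With skewed scores its size is uncertain, though its direction was the same throughout.

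**What to change.** Before outcome data are analysed, pre-specify a key analysis of the EPDS total score beside the logistic analysis of scores above 12. Use linear regression with robust standard errors, or ordinal regression on the score, with the same covariates as the logistic model. Use the full-score analysis for the interaction terms and for food security severity on this outcome. State that severity enters as the exposure and the EPDS as the dependent variable.

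The cost is analysis-plan wording, recorded as a dated addition because data collection has begun. No new data, participants or procedures are needed. The downside is that a mean difference in score is less direct clinically than a difference in the proportion with depression; the retained analysis above 12 supplies that. Because that analysis stays in place, the definition of the primary outcome does not change.
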